#### Tonic timescale.

***Mood change analysis:*** To assess changes in mood over time (Hypothesis 3), we will use linear mixed-effects models (LMMs), treating time (pre vs. post) and condition (co-rumination vs. natural sharing) as fixed effects, and including random intercepts for participants nested within dyads to account for the non-independence of dyadic partners and repeated measurements. This approach enables us to examine overall mood changes without splitting sharers and supporters into separate analyses.

For Hypothesis 5, we will examine whether mood following co-rumination differs from mood following natural sharing using the same LMM framework, focusing on post-sharing mood scores across conditions.

***Emotional appraisal analysis:*** To evaluate changes in emotional appraisals (Hypothesis 4), we will calculate change scores by subtracting the pre-sharing appraisal rating from the post-sharing appraisal rating for each emotional episode. These change scores will then be entered into linear mixed-effects models, with condition as a fixed effect and random intercepts for participants nested within dyads. This approach accounts for within-person and within-dyad dependence and avoids the use of separate t-tests for each condition. Hypothesis 6 will be tested by comparing appraisal change scores between the co-rumination and natural sharing conditions using the same dyadic LMM framework.

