### Emotional sharing task

The emotional sharing task, which is modelled after Nils & Rimé (2009), involves a structured procedure to make participants share their emotions in a controlled experimental setting [13]. Participants will be having a total of four eight-minutes episodes with their partner to share the two experiences they each wrote down in the experience generation task. During each episode, one participant will act as a sharer (to discuss the problem) and the other participant will act as a supporter (to listen and respond to the sharer). The roles of sharer and supporter will be randomly alternated so that each participant will be a sharer and a supporter twice.

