### Co-rumination manipulation

We will experimentally manipulate the instructions of the emotional sharing task, following a validated procedure developed by Tudder et al (2023) [27]. For half of the sharing episodes, the supporter will receive instructions that promote co-rumination, which involves focusing on a topic, repeatedly discussing the issues, speculating about the antecedents and consequences of the issues, and exploring and unearthing negative emotions. For the other sharing episodes, the supporter will be instructed to respond in a natural way to the sharer. The order of the co-rumination versus natural response will be counterbalanced. Each member of the couple will be instructed once to engage in co-rumination and once to engage naturally with the sharer in all four conditions, the participants will receive digital instructions and physical cards to remind them of their role and the associated instructions.

Before the first sharing episode, participants will be taken by their experimenter to the emotional sharing space with the two armchairs (see Fig 1b), so that they can familiarize themselves with this space Then they will be taken back to their private space, where they will be informed about the first experience to address and be asked to “collect their thoughts” for two minutes. Following this, each participant will again be taken to the emotional sharing space. Participants will then engage in their first round of emotional sharing on the selected experience. After completing the first emotional sharing episode, the participants will go back to the private space and complete the post-dialogue survey about their sharing experience. After completing the first instruction, the instructions for natural sharing and co-rumination will be reversed, and after two rounds, the roles of the sharer and supporter will be switched, and vice versa.

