### Measurement

Table 2 provides a comprehensive overview of the tools and objectives for the measurement employed in this study. More detailed information can be found in Supplementary 2 in S1 File.

**Table 2 pone.0323526.t002:** Overview of the measurement tools, objectives and measurement period.

Timescale	Name	Measurement objectives	Measurement period
*Phasic*	VRMS	Movement synchrony	Emotional sharing episodes
	CMS	Cardiovascular synchrony	Emotional sharing episodes
*Tonic*	BEF	Mood (e.g., *“Helplessness.”)*	Pre-sharing survey and post-dialogue surveys
	ES	Emotional Appraisal (e.g., *“How intense were the negative emotions that you had during this experience?”*)	Pre-sharing survey and post-dialogue surveys
	IOSS	How close the respondent feels with another person (seven images)	Pre-sharing survey and post-dialogue surveys
	SOE	The experiences of partners in conversation (e.g., *“I felt completely like myself during the conversation.”*)	Post-dialogue surveys
	PPR	Individuals’ perceptions of their partners’ responsiveness (e.g., *“My partner understood me.”*)	Post-dialogue surveys
	IER-DSFP	Different interpersonal emotion regulation strategies from partner (e.g., *“My partner tried to get me to talk over and over about what is bothering me.”*)	Post-dialogue surveys
	RQ-ASSC	Relationship quality (e.g., *“My partner and I agreed on how I could best approach the problem.”*)	Post-dialogue surveys
*Chronic*	DCI	Dyadic coping strategies (e.g., *“I tell my partner that it is not that bad and help him/her to see the situation in a different light.”*)	Pre-sharing survey
	PQ-SF	Quality of romantic relationships (e.g., *“He/she takes me in his arms.”*)	Pre-sharing survey
	PSAS-SF	Attachment styles (e.g., *“It helps to turn to my partner in times of need.”*)	Pre-sharing survey
	TAS-20	Alexithymia (e.g., *“I am often confused about what emotion I am feeling.”*)	Pre-sharing survey
	OSRS	Participants’ perception of emotion regulation (e.g., *“I gave someone helpful advice to try to make them feel better.”*)	Pre-sharing survey
	SSL	Perceived social support received (e.g., *“Did you ask for help or advice?”*)	Pre-sharing survey
	SV	Sociodemographic variables (e.g., *“How old are you*.*”*)	Post-sharing survey
	UCLA-LS	Loneliness (e.g., *“I lack companionship.”*)	Post-sharing survey
	IRI	Empathy (e.g., “*I sometimes find it difficult to see things from the other person’s perspective*.”)	Post-sharing survey

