#### Chronic timescale.

***Relationship quality and dyadic coping analysis:*** We will employ regression analysis to examine the associations between relationship quality and dyadic coping strategies and movement and cardiovascular synchrony (*Hypothesis 7.1 and 7.2*). Additionally, to analyse whether dyadic coping and relationship quality are associated with mood changes we will add these variables as fixed factors in the linear mixed models built for testing hypothesis 3 on mood change over time (*Hypothesis 7.3*). Linear regression analyses will also be used to assess whether relationship quality and dyadic coping are related to emotional appraisal change (*Hypothesis 7.4*).

To assess whether co-rumination versus natural sharing influences the relationship between higher relationship quality and more constructive dyadic coping and movement and cardiovascular synchrony moderated regression analyses will be used (Hypotheses 8.1 and 8.2). To analyse whether the associations between relationship quality and dyadic coping with mood change are associated with effects of co-rumination versus natural sharing we will extend the linear mixed models used for testing hypothesis 7.3. The full model will consist of a random intercept for participants, fixed factors of assessment time and condition, their interaction, and mood as the dependent variable (*Hypothesis 8.3*). Moderated linear regression analyses will be used to assess whether better relationship quality and dyadic coping are associated with weaker effects of the co-rumination condition versus natural sharing on emotional appraisal change (*Hypothesis 8.4*).

The hypotheses presented in Table 1 and the data analysis techniques utilized constitute the core elements of our research. Additionally, we have identified and measured a range of secondary variables that could potentially influence these associations. Our aim is to incorporate these variables as covariates in the analyses to enhance our understanding of the findings. For all statistical tests α ≤ 0.05 (two-tailed) will be applied. Given the wide range of statistical tests performed, there is a concern regarding multiple comparisons. Therefore, to reduce the likelihood of Type I errors, we will apply the Bonferroni correction to all previously mentioned test results.

***Exploratory analyses summary:*** In our study, we plan to conduct exploratory analyses to investigate interpersonal synchrony in verbal communication:

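### The H3 pre-post mood test has random intercepts only, so its standard error is too small if people or couples differ in how much their mood changes

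*Protocol article*

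**What the plan says.** Under Tonic timescale, the H3 mood model is fixed as "treating time (pre vs. post) and condition (co-rumination vs. natural sharing) as fixed effects", "including random intercepts for participants nested within dyads to account for the non-independence of dyadic partners and repeated measurements". No random slope for time, dyad-level change effect or residual correlation is named.

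The number of ratings has to be pieced together. Table 2 gives the mood checklist's timing as "Pre-sharing survey and post-dialogue surveys". The Emotional sharing task section says "Participants will be having a total of four eight-minutes episodes with their partner". The Co-rumination manipulation section says that after the first episode "the participants will go back to the private space and complete the post-dialogue survey about their sharing experience". Together these give one pre and four post ratings per participant.

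Under Chronic timescale, relationship quality and dyadic coping enter for H7.3 as follows: "we will add these variables as fixed factors in the linear mixed models built for testing hypothesis 3 on mood change over time". For H8.3, "The full model will consist of a random intercept for participants, fixed factors of assessment time and condition", plus their interaction.

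**The concern.** A random-intercept model implies one common correlation among a person's five ratings. That is the same as saying everyone's true mood change is equal, with only rating noise on top. If some people improve more than others, the excess appears in all four of that person's post ratings. If partners improve together, it appears in all eight of the couple's. Averaging the post ratings removes rating noise but not this shared change, and the model's standard error for time does not allow for it.

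The article gives reason to expect such variation. H7 in Table 1 predicts that mood change depends on relationship quality and dyadic coping, and the introduction expects these to matter much more for mood change than the manipulation does. The H3 model contains neither those covariates nor a slope to carry the variation. H3 is a main confirmatory hypothesis, so it could be declared supported at a true error rate above the stated one.

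**Working it through.** **Plan's own figures.** The article states no error rate, slope variance or residual variance for the mood model. Its sample size figure does reproduce: for an effect of 0.5, two-sided 0.05 and two independent groups, the exact t calculation gives 64 per group, 128 in total, power 0.801. That figure does not enter the check below, because the variance ratio does not depend on the number of couples.

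**Inputs from the article.** One pre rating, K = 4 post ratings, 150 couples, two-sided alpha 0.05, random intercepts only.

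**Assumed, because the article is silent.** q = between-person variance of true change divided by residual variance s², varied from 0 to 2. ρ = partner correlation of true change, varied from 0 to 0.5.

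**Formulas**, for the contrast mean post minus pre, averaged over partners and up to a common factor:

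- True variance: q(1 + ρ) + 1 + 1/K.
- Variance the model reports: (1 + q/(K + 1))(1 + 1/K). The first bracket arises because only q/(K + 1) of the change variance leaks into the estimated residual variance.
- Actual error rate: 2[1 − Φ(1.96/√ratio)], where ratio is the true variance divided by the reported variance.

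**Worked case, q = 1, ρ = 0.** True: 1 + 1 + 0.25 = 2.25. Reported: 1.2 × 1.25 = 1.5. Ratio 1.5, and 1.96/√1.5 = 1.60, so the rate is 11.0%.

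| q | ρ = 0: ratio, rate | ρ = 0.3: ratio, rate | ρ = 0.5: ratio, rate |
|---|---|---|---|
| 0 | 1.00, 5.0% | 1.00, 5.0% | 1.00, 5.0% |
| 0.25 | 1.14, 6.7% | 1.20, 7.4% | 1.24, 7.8% |
| 0.5 | 1.27, 8.2% | 1.38, 9.5% | 1.45, 10.4% |
| 1 | 1.50, 11.0% | 1.70, 13.3% | 1.83, 14.8% |
| 2 | 1.86, 15.0% | 2.20, 18.6% | 2.43, 20.9% |

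**Simulation check** (150 couples, 2,000 runs per setting, nested random-intercept fit, time effect averaged over conditions). The rate was 5.4% at q = 0. At q = 1 it was 10.9%, 12.7% and 14.8% for ρ = 0, 0.3 and 0.5. At q = 2, ρ = 0.3 it was 19.3%. If the pre rating is coded as natural sharing, so that time means the change under natural sharing, the q = 1 rates were 10.1%, 11.5% and 12.8%.

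**Comparator.** In a separate simulation with pre-post correlation 0.5 and post-post correlation 0.7, the written model gave 12–15%. A test on couple-level change scores gave 4.5–5.2%.

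**Bonferroni.** The number of tests is not stated. Assuming 8, the per-test level is 0.05/8 = 0.00625. At q = 1 the actual rate is then 4.1 to 7.0 times that, or 0.026 to 0.043. At q = 2 it is 0.045 to 0.079.

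**H7.3.** As a main effect, which is how it is written, the simulated rate was 4.2–6.2%, which is nominal. As a quality-by-time term it was 6.8% at q = 0.25, 8–9% at 0.5, 11–12% at 1 and 17.5% at 2.

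**H8.3.** Condition varies among the same person's post ratings, so a shared change cancels from that contrast. The simulated quality-by-condition rate, at ρ = 0.3, was 4.8%, 3.7%, 3.7% and 1.9% at q = 0, 0.67, 1 and 2.

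**The case against.** **The size is not in the documents.** A reader might infer that the error rate is simply two to four times nominal. The article gives no correlations and cannot support one figure. With no variation in change there is no inflation, and at q = 0.25 it is only 1.3 to 1.6 times. This stands, so the result is given as a range.

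**The layout is inferred.** The article defines time only as pre versus post and does not say how the post ratings enter. With a single post rating per person, inflation vanishes at ρ = 0 and is at most about 1.8 times for q up to 4 and ρ up to 0.5. Four post ratings remain the natural reading.

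**Bonferroni lowers the threshold.** With 8 assumed tests, the H3 rate at q = 1 stays below 0.05 in absolute terms. That is true, but the test still exceeds the level it was allotted, and the relative excess grows as alpha shrinks.

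**Detail may sit in the supplement or a SAP.** Random-slope detail is often left there. Here, however, the article states the random structure and claims that it handles the repeated measurements, and that claim is incorrect for the pre-post effect.

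**H7.3 and H8.3.** A reader might infer that both are inflated as written. No time interaction is written for H7.3, and its main effect keeps its level, though it addresses mood level and not mood change, which is a separate matter. For H8.3, a reader might also infer that the dyad level has been removed. The article says that model extends the H7.3 one, which builds on the nested H3 model, so a shortened description is at least as plausible.

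**Conclusion.** The point holds for H3. The stated random-intercept structure does not account for the repeated measurements when the pre-post effect is tested, and the standard error is too small whenever true mood change varies between people or couples. At nominal 5% the error rate is about 7–8%, 8–10%, 11–15% and 15–21% for change variance of 0.25, 0.5, 1 and 2 times residual variance. It is 5% if there is no such variation. These figures assume one pre and four post ratings, equal residual variance, no serial correlation and a partner correlation of change between 0 and 0.5.

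H7.3 is affected only if a quality- or coping-by-time term is tested. Inflation is not shown for the H8.3 condition contrast. A reader might also suppose that the single pre rating will be repeated as the baseline row of each dialogue. The documents do not say so, and no conclusion here rests on it.

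**What to change.** In the H3 model, add random slopes for time (post versus pre) by participant and by dyad, and state that the single pre rating enters once. If the fit is singular, test one change score per couple against zero: the mean of the post ratings minus pre, averaged over partners. The article already uses change scores for appraisals, so this fits its own approach. Use the same error structure for any quality- or coping-by-time term. Delete the statement that random intercepts alone account for the repeated measurements.

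The cost is wording and model code, with no change to design or data collection. The downside is wider intervals and occasional convergence handling.

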## Methods and statistical analysis

### Design

This study has a mixed factorial-experimental nested design. In total, each couple engages four times in the emotional sharing task, twice in the co-rumination and twice in the natural sharing condition. Each participant will twice share a distressing experience and will twice act as supporter. Both aspects will be experimentally manipulated between participants. Measures of mood and appraisal will be nested within participants, while movement and cardiovascular synchrony will be nested within dyads. The chronic variables (i.e., dyadic coping and relationship variables) will be used correlational.

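### The mood model's dyad and person intercepts do not cover partner dependence within a dialogue, so alpha for the co-rumination contrast (H5, and the condition terms of H8.3) is not assured

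*Protocol article*

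**What the plan says.** The Design section states that "each couple engages four times in the emotional sharing task, twice in the co-rumination and twice in the natural sharing condition". Under Co-rumination manipulation the condition is set per episode: "For half of the sharing episodes, the supporter will receive instructions that promote co-rumination". After the dialogue, "the participants will go back to the private space and complete the post-dialogue survey about their sharing experience", and Table 2 places the mood checklist in the pre-sharing survey and in the post-dialogue surveys. Each dialogue therefore yields two post-dialogue mood ratings, one per partner, under one shared condition.

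For H3 the Mood change analysis describes linear mixed models. Their fixed part is given as "treating time (pre vs. post) and condition (co-rumination vs. natural sharing) as fixed effects". Their random part is described in these words: "including random intercepts for participants nested within dyads to account for the non-independence of dyadic partners and repeated measurements". On pooling the two roles, the section adds: "This approach enables us to examine overall mood changes without splitting sharers and supporters into separate analyses". H5 is tested "using the same LMM framework, focusing on post-sharing mood scores across conditions".

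For H8.3 the Chronic timescale section says the models for H7.3 will be extended, and then: "The full model will consist of a random intercept for participants, fixed factors of assessment time and condition". No dyad term is named there. Neither section gives the mood model a dialogue-level term, a correlation between the partners' residuals within a dialogue, or a fixed effect for sharer/supporter role.

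**The concern.** A dyad intercept captures what two partners share over the whole session, and a person intercept captures what is stable in one person. Neither captures a particular conversation that went well or badly for both. Condition varies at exactly that level, from one conversation to the next within a couple. The stated model therefore counts two ratings of one dialogue as two independent replicates of the condition, while the text says partner dependence has been dealt with.

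At stake is the standard error of the co-rumination effect on mood. H5 is one of the main confirmatory hypotheses in Table 1, and the Discussion identifies co-rumination as the one process that is manipulated experimentally. The study's premise, that partners regulate each other's emotions during a conversation, makes zero within-dialogue covariance an awkward thing to assume silently.

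**Working it through.** **The plan's own figure.** For two independent means with d = 0.5, two-sided alpha 0.05 and 80% power, the normal approximation gives 2 × (1.960 + 0.842)² / 0.5² = 62.8, so 63 per group. The exact t calculation gives 64 per group, 128 in total, with power 0.801. The stated 128 reproduces, but it carries no information on r.

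**Inputs.** From the protocol: 150 couples, 4 dialogues each (2 per condition), 2 ratings per dialogue, each person sharer twice and supporter twice, alpha 0.05 two-sided. That makes 600 dialogues and 1,200 post-dialogue ratings, 600 per condition. Assumed, because the protocol gives neither: the same-dialogue residual correlation r, and the sharer–supporter mood gap g in residual SD.

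**Step 1: the intercepts cancel.** Each person rates two co-rumination and two natural dialogues. A constant for the person or the couple enters both condition means equally and drops out of the difference.

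**Step 2: model against truth, no role effect.** With residual variance 1, the stated model gives Var = 1/600 + 1/600 = 2/600, so SE = 0.0577. With partners correlated at r inside a dialogue, the true variance is 2(1+r)/600. The ratio of true to model SE is sqrt(1+r), and the actual type I error is 2 × [1 − Φ(1.96 / sqrt(1+r))].

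| r (assumed) | true SE / model SE | type I error at nominal 5% |
|---|---|---|
| −0.2 | 0.89 | 2.8% |
| 0 | 1.00 | 5.0% |
| 0.1 | 1.05 | 6.2% |
| 0.2 | 1.10 | 7.4% |
| 0.3 | 1.14 | 8.6% |
| 0.5 | 1.22 | 11.0% |

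A simulation of this layout (4,000 replicates per setting) gave 2.9%, 4.7%, 6.6%, 7.6%, 9.2% and 12.0% for the same values of r. Analysing at the dialogue level held 4.7% to 5.4% throughout.

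**Step 3: role left out, as in the stated fixed effects.** Each dialogue pairs a sharer with a supporter. Role shifts each rating by ±g/2 and averages to zero within a person. It adds 4 × (g/2)² to each person's residual sum of squares on 3 degrees of freedom, so the model's residual variance becomes 1 + g²/3. The ratio is then sqrt[(1+r) / (1 + g²/3)]. For r = 0.3:

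| g (assumed) | true SE / model SE | type I error, formula | type I error, simulation runs |
|---|---|---|---|
| 0.5 | 1.10 | 7.4% | 7.0–7.4% |
| 1.0 | 0.99 | 4.7% | 4.0–5.3% |
| 1.5 | 0.86 | 2.3% | 1.9–2.5% |

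The model SE is too small only when r exceeds g²/3. At r = 0.3 the break-even gap is sqrt(0.9) = 0.95 residual SD. With r = 0.3, g = 1.0 and role in the model, simulated type I error was 8.4%, in line with Step 2.

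**Step 4: H8.3.** For moderation of the condition effect by individual scores that correlate at m between partners, the factor is sqrt(1 + r·m). Since m is at most 1, the Step 2 figures for positive r are an upper bound there.

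**The case against.** The strongest reply is that the protocol gives neither r nor the role gap. A reader might infer that the confidence intervals are too narrow as planned. The documents do not support that: at r = 0 the SE is right, at negative r it is too wide, and with role omitted a gap near one residual SD cancels the error at r = 0.3 while a larger one reverses it. This stands and limits the point to a conditional one. It does not rescue the model, because two unmodelled quantities that happen to offset each other give no control of alpha.

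The reply also holds on scope. H3 is a time effect and H7.3 concerns associations with relationship measures. Neither is a condition contrast, and no harm is shown for them. A reader might also infer that the missing dyad term in the H8.3 sentence itself distorts the condition SE. It does not, because a dyad intercept cancels from that contrast. The wording may be shorthand, since the model is said to extend the one for H7.3.

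Bonferroni correction means 5% is not the level actually used. At an illustrative 0.05/16 = 0.31% (the number of tests is an assumption), r = 0.1 and 0.3 give 0.48% and 0.95% under Step 2. The absolute excess is under one percentage point but the ratio to nominal is larger, so the correction does not repair the problem.

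Finally, a condensed article may leave model detail to an analysis plan. That would answer a complaint of missing detail. Here the article states the random structure and states what it achieves, and for H5 the second statement does not follow from the first. The Chronic timescale section promises covariates from the secondary variables but does not name role.

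**Conclusion.** The point holds in conditional form. For the co-rumination contrast on mood, intercepts for participants nested within dyads do not account for partner non-independence within a dialogue, contrary to the text. With role absent or modelled, H5's type I error at nominal 5% runs from 5.0% at r = 0 to 6.2%, 8.6% and 11.0% at r = 0.1, 0.3 and 0.5, and falls below 5% for negative r. With role omitted, as stated, the error can go either way. For H8.3 these values are upper bounds. They rest on assumed r and g, full balance, and 150 complete couples. The consequence is modest but affects a main confirmatory test, and it is cheap to remove.

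**What to change.** In the H5 and H8.3 mood models:

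- Add sharer/supporter role as a fixed effect.
- Add a random intercept for dialogue within dyad, or let the two partners' residuals correlate within a dialogue. The second option also allows negative r, which a random intercept cannot represent.
- Make both changes together. With r = 0.3 and role left out, simulation put the dialogue variance at zero in about 71% of trials at a gap of 1.0 residual SD, and in all of them at 1.5. The dialogue term alone would then change nothing.
- Where a model includes the single pre-sharing mood rating, code it as its own occasion, since it belongs to no dialogue.
- State the same random structure in the Chronic timescale section as in the Tonic timescale section, and reword the claim about partner non-independence to match.

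The cost is one variance (or correlation) term and one covariate, with possibly slightly wider intervals. No new data are needed.

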**Fig 2 pone.0323526.g002:**
[figure not shown]
Photograph of the emotional sharing space and one individual workspace.

In the first phase of the experiment, participants will be asked to rate their mood on the mood adjective checklist (BEF) [24]. Then they will be instructed to generate two personal negative experiences using the Experience-Generation Questionnaire (EGQ) [25]. Subsequently, the Experience Scales (ES) [26] will be used to tap into their appraisal of these two experiences. Next, participants will be fitted with the sensors of the Vrije Universiteit - Ambulatory Monitoring System (VU-AMS). Once the VU-AMS has been set up, participants will be requested to complete the pre-sharing survey.

Subsequently, participants will be provided with instructions for the emotional sharing task, consisting of four dialogues. Upon completion of the entire emotional sharing task, participants will complete a post-sharing survey and the ECG device will be removed. Finally, participants will be debriefed, rewarded, and thanked. Fig 3 shows the whole experimental session. In total, the experiment takes approximately 2 hours, with task instructions taking 10 minutes, device fitting taking 15 minutes, the pre-sharing survey taking 15 minutes, the emotional sharing task for four episodes lasting 60 minutes, the post-sharing survey taking 15 minutes, and the device removal and closure taking 5 minutes.

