### Experiences generation task

In the emotional sharing tasks, participants will be asked to talk about two negative experiences from their own life. To illustrate what is meant by negative experiences, the ERQ lists seven negative experiences, such as having an argument with a close friend or family member. Participants will be asked to write down two negative experiences they are currently facing. By focusing on personal experiences, we ensure that the study has high personal relevance for the participants.

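### The H6 appraisal contrast ignores each experience's own pre-sharing rating and so gives up precision that the collected data could supply

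*Protocol article*

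**What the plan says.** All references are to the Protocol article.

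- **Two experiences per person.** Experiences generation task: "Participants will be asked to write down two negative experiences they are currently facing".
- **Both rated beforehand.** Procedure: "Subsequently, the Experience Scales (ES) [26] will be used to tap into their appraisal of these two experiences".
- **Condition crossed within sharer.** Under Co-rumination manipulation, each partner, as supporter, gives one co-rumination episode and one natural episode. Each sharer therefore has one experience under each instruction. Instruction order is counterbalanced. Of the participants it says that "they will be informed about the first experience to address"; it does not say how an experience is matched to an instruction.
- **Outcome.** Tonic timescale: "we will calculate change scores by subtracting the pre-sharing appraisal rating from the post-sharing appraisal rating for each emotional episode".
- **Model.** "These change scores will then be entered into linear mixed-effects models, with condition as a fixed effect". The only other term named is a random intercept for participants within dyads.
- **H6.** "Hypothesis 6 will be tested by comparing appraisal change scores between the co-rumination and natural sharing conditions using the same dyadic LMM framework".
- **Other covariates.** Chronic timescale foresees covariates drawn from the secondary variables. Appraisal is a primary outcome according to the Abstract, so its pre-sharing rating is not among them on a plain reading.

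**The concern.** The within-subject design makes the two conditions comparable with respect to the person, but not with respect to the experience. A sharer's two experiences may start at different intensities. Whenever the slope of the post-rating on the pre-rating is below 1, the expected change depends on the starting value.

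Two features of the plan might seem to deal with this, but neither does. The participant intercept absorbs what a sharer's two episodes have in common and leaves the difference between them. Counterbalancing the order guards against a systematic tilt and does not remove random differences in severity.

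At stake is the precision of H6, which predicts smaller appraisal changes under co-rumination, and of the condition-by-moderator interaction in H8.4. All tests are also to be Bonferroni-corrected, so lost precision costs more than it would at 0.05.

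**Working it through.** **The plan's own figure.** Sample size determination gives 128 for two independent means, effect 0.5, 80% power, two-sided 0.05. The normal approximation gives 63 per group (126). The exact t calculation gives 64 per group (128, power 80.1%). The figure reproduces, but it is not a power calculation for H6, and the article gives none.

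**Inputs for the check.** The target of 150 dyads gives 300 sharers with two experiences each. Assumed, because the documents do not give them: equal pre and post standard deviation s, and a within-person, across-experience pre-post correlation r between 0.3 and 0.9. Correlation between partners is ignored.

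**Variance per episode.**
- Raw change: 2s²(1 − r).
- Adjusted for the pre-rating: s²(1 − r²) = s²(1 − r)(1 + r).
- Ratio, adjusted to raw: (1 + r)/2.

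**Power.** If raw change has 80% power at two-sided 0.05, its non-centrality is 1.960 + 0.842 = 2.802. Adjusted power is Φ(2.802/√ratio − 1.960). At r = 0.5 this is Φ(2.802/0.866 − 1.960) = Φ(1.275) = 89.9%.

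| r | Variance ratio | Extra sharers raw change needs (1/ratio − 1) | Adjusted power |
|---|---|---|---|
| 0.3 | 0.65 | 54% | 93.5% |
| 0.5 | 0.75 | 33% | 89.9% |
| 0.7 | 0.85 | 18% | 86.0% |
| 0.9 | 0.95 | 5% | 82.0% |

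**Chance imbalance.** The mean pre-rating difference between conditions has standard deviation √(2/300) = 0.082, in units of s. The change score already subtracts the pre-rating with coefficient 1, so only (1 − r) of the imbalance remains in the estimate. The standard error of the raw contrast is √(4(1 − r)/300).

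| r | Shift for a 1-SD imbalance, (1 − r) × 0.082 | Standard error of raw contrast |
|---|---|---|
| 0.3 | 0.057 | 0.097 |
| 0.5 | 0.041 | 0.082 |
| 0.7 | 0.024 | 0.063 |
| 0.9 | 0.008 | 0.037 |

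The share of the contrast's variance that comes from imbalance is (1 − r)²(2/300) ÷ [4(1 − r)/300] = (1 − r)/2, or 35%, 25%, 15% and 5%. That equals 1 minus the variance ratio. Chance imbalance and lost precision are therefore one problem, not two.

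**Simulation** (300 sharers, two experiences each, 4000 runs, random allocation). Both estimators averaged close to zero under no effect. The variance ratios were 0.67, 0.76, 0.84 and 0.96. The raw contrast correlated with the imbalance at −0.58, −0.50, −0.41 and −0.20. After adjustment the correlation was about zero.

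**Why H7.4 differs.** Relationship quality and dyadic coping are measured, not assigned. Suppose there is no true change, quality lowers true severity with slope −0.4, and the ratings have reliability 0.64 at a given level of quality. The change-score slope on quality is 0. The baseline-adjusted slope is −0.4 × (1 − 0.64) = −0.14, an association created by the adjustment. In H8.4 this artefact is the same under both instructions and cancels from the interaction, provided allocation ignores severity and the pre-post slope does not depend on condition.

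**The case against.** The strongest reply is that nothing here is invalid. H4 and H6 are worded as changes, and a change score tests change. The contrast is unbiased under allocation independent of severity, and its standard error already includes the random differences in severity. All of that stands, so the point concerns efficiency only.

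The size may also be small. The same experience is re-rated within a session of about two hours, and the example ES item asks about emotions felt during a past event. Both make a high r plausible, and at r = 0.9 the gain is 5% in variance. In addition, take the protocol's planning effect of 0.5 in change-score standard deviations, with 300 sharers and no within-person correlation. The planned contrast then has non-centrality 0.5/√(2/300) = 6.1 and power above 99.9% at 0.05. The loss would then matter only for effects smaller than 0.5, or for the interaction. This stands too, as a limit on importance. It is no reason to leave a collected baseline value unused.

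A reader might infer three stronger claims, none of which the documents support:

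- **That severity systematically confounds H6.** Order is counterbalanced, and nothing says that severity decides which experience goes with which instruction. The article does not describe the matching, but such detail is commonly left to the full protocol.
- **That a severity imbalance passes in full into the estimate.** Only the fraction (1 − r) does.
- **That every appraisal model should be baseline-adjusted.** For H7.4 this would change the question and could create an association. The introduction itself expects better-functioning couples to have worked on their problems already, so their starting appraisals may well differ.

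**Conclusion.** The concern holds as a loss of precision in H6 and in the H8.4 interaction, not as bias. The planned model is stated in the article, so this is a choice that can be improved rather than a detail left to another document. The loss is moderate if r lies between 0.3 and 0.7 (15% to 35% of the variance) and slight at 0.9 (5%). These figures rest on the assumed r, on equal pre and post variances, and on allocation of experiences independent of severity. The 80% starting point for power is an illustration and not a figure from the plan. The change is worth making, but the analysis remains valid without it.

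**What to change.** In the H6 model, add the pre-sharing ES rating of the experience discussed as two fixed covariates: the sharer's mean over both experiences (grand-mean centred) and the deviation of this experience from that mean. The deviation carries the gain for the condition contrast. The split keeps within-person and between-person slopes from being pooled into one coefficient.

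Use the same two terms in the H8.4 model, and interpret only the condition-by-moderator interaction from it. Keep the unadjusted change score for H4 and H7.4.

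The cost is one or two extra model terms. No new data and no added burden on participants are needed. The gain will be small if r turns out to be high.
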